### Clinical outcomes

#### Primary outcome

The primary outcome is the frequency and severity of self-injurious episodes, measured by the Suicide Attempt Self-Injury Interview (SASII [63]). The SASII is a semi-structured interview that measures frequency and medical severity of self-injury and suicide attempts and is administered by trained assessors at all assessment points to measure self-injury over the previous 3-month assessment interval.


The following other measures are administered to assess predictors of response. Demographic information will be collected with the Demographic Data Schedule (DDS [82]) at baseline. The NEO-Five Factor Inventory, short form (NEO-SF [83]), a widely used personality measure, is being used to assess personality dimensions (i.e., neuroticism, extraversion, openness, agreeableness, and conscientiousness) and is collected at baseline. The Childhood Trauma Questionnaire-Short Form (CTQ-SF [84]), a self-report measure of childhood abuse and neglect is being collected at 3-months and the Credibility/Expectancy Questionnaire (CEQ [85]) is being collected at baseline. The Working Alliance Inventory-Short Form (WAI-S [86]), therapist and client version are collected after each of the first 4 treatment sessions and at 3 and 6-months.

Finally, the Reasons for Early Termination from Treatment Questionnaire (RET-C [87]) is administered to evaluate reasons for premature termination and is administered to participants who drop out of treatment.

Participants are being compensated at a rate of $10 Canadian dollars (CDN) per hour for the completion of these study measures.

#### Health economic outcomes

One objective of this research is to compare the cost of DBT-6 vs DBT-12. Costs include direct treatment cost, health services cost (e.g., hospitalization, emergency room visits, day surgery or procedure, physician visits, medications), productivity costs, and law enforcement and related cost. The cost analysis will be based on the healthcare resources data obtained from the THI-2 in the trial and with participant consent, imported to and linked with federal and provincial administrative databases (for Ontario, the Institute for Clinical Evaluative Sciences; for British Columbia, B.C. Population Health; in addition to the Canadian Institute for Health Information). Additionally, using established guidelines for cost-effectiveness research [88], data on therapist and consultation team time devoted to research participants (e.g., in meetings, individual and group sessions, between-session communication) are being collected and used to calculate per patient cost of service provision based on expected service provider costs (e.g., salary, benefits).

#### Genetic data

An amendment to the original protocol for the addition of a genetic component to the study and collection of saliva samples was approved in September, 2015. A separate consent form was developed for this data collection. Participants’ who provide consent to the genetic study are required to provide five small saliva samples (about half a teaspoon each) to the research team at the following time points: a) at baseline, b) at 6-months, c) 1 year, d) one-and-a-half years, and e) 2 years into the study. These time-based samples will be used specifically for epigenetic comparisons before, during and after DBT treatment. Patients are receiving $20 remuneration per saliva sample.

Data collection for the study began in February, 2015 and is expected to be complete by July, 2019.

Interview outcome data will be double data-entered. Other data collected via an electronic encrypted data management system are not double data entered. Data is stored on an encrypted server. Study outcome data is stored in a locked cabinet in accordance with ethical guidelines governing the management of data. All study data collected will be maintained for 25 years before being destroyed.

### Sample size and power analysis

The study was designed to test whether DBT-6 is not inferior to DBT-12 (an established treatment). The estimate of the sample size required for a non-inferiority test was based on the effect sizes from prior DBT RCTs [30, 62]. Post-treatment suicide and self-harm estimates over 4 months were 2.26 episodes for DBT-6 and 0.73 for DBT-12 (SD_pooled_ = 4). We expected no significant differences between the DBT-6 and DBT-12 conditions in terms of reductions in the frequency and severity of self-injury episodes at 1 year. We therefore defined our delta, the clinically significant range of indifference for our non-inferiority trial, as a difference in outcomes of 1.53 (SD = .04) episodes in the frequency of self-harm episodes at post-treatment. To achieve this maximum of 1.53 or less in the difference of self-injury rates with adequate power (α = .05; 1 - β = .80), 85 participants per group are required to show non-inferiority of treatment. Allowing for a 30% dropout rate, we will recruit 120 participants per group. The sample size calculation also addresses the necessary power for secondary analyses, given that the sample size required for null hypothesis significance testing is typically less than those required for non-inferiority [89].

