#### Primary analyses

##### Comparison of DBT-6 versus DBT-12

Analyses will be conducted at the end of treatment and at the end of follow-up. No interim analyses are planned. The outcome analyses will be conducted on an intention-to-treat basis. The primary outcomes, frequency and severity of suicide and self-harm behaviours, are both expected to have a skewed distribution. The count nature of the self-injury frequency variable, as well as the self-injury severity ratings, are integers bounded by zero. As well, given the dependencies of the observations over time and individual variability, our primary analyses will employ a multilevel random effects Poisson growth curve model. The occasion level random effects will capture secondary over-dispersion due to the heterogeneity of observations within participant self-injury reporting [88, 90]. These random effects will follow a log-normal distribution [91], and will reduce or eliminate the disturbance effects associated with the differences between rates and forms of specific, within individual, self-harm that can bias estimates of true self-harm rates.

Specific tests of our primary hypotheses (non-inferiority tests of equivalence and post hoc comparisons of difference) will be model-based [92] using contrasting means and regression coefficients. Evaluation of model fit will be provided by statistical indices including Akaike’s Information Criteria (AIC) and Bayesian Information Criteria (BIC) and likelihood ratio tests. To perform the comparison of self-injury outcomes at post-treatment (our primary research interest), 1-sided non-inferiority t-tests of the marginal means will be performed. If missing data are at moderate levels or are related to a specific set of covariates or outcome, we will compare multiple imputation [93], growth curve analysis [94], and instrumental variables analysis [95] since no one technique is demonstrably superior [96]. We will also examine differences in sites and therapist characteristics that may be evidenced in treatment outcomes.

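### The non-inferiority margin of 1.53 episodes comes from 4-month counts but is stated without a time unit, while the primary outcome counts episodes over 3 months; the two are never put on one scale.

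*Protocol article*

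**What the plan says.** In the protocol article, Sample size and power analysis gives the planning figures as "Post-treatment suicide and self-harm estimates over 4 months were 2.26 episodes for DBT-6 and 0.73 for DBT-12", with a pooled SD of 4. It then defines the margin "as a difference in outcomes of 1.53 (SD = .04) episodes in the frequency of self-harm episodes at post-treatment". That sentence gives no time window, and its SD differs from the pooled SD in the same paragraph by a factor of 100. The design values are "α = .05; 1 - β = .80", and the result is that "85 participants per group are required to show non-inferiority of treatment".

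Under Primary outcome, the SASII is "administered by trained assessors at all assessment points to measure self-injury over the previous 3-month assessment interval". Table 1 gives the same 3-month window, and visits are 3 months apart up to 24 months.

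The section Comparison of DBT-6 versus DBT-12 states how the margin is used: "1-sided non-inferiority t-tests of the marginal means will be performed", at post-treatment, from a multilevel Poisson growth model. It does not say what length of time a marginal mean refers to.

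**The concern.** The margin decides whether the shorter treatment is called non-inferior. A margin on an episode count has meaning only together with the period over which episodes are counted. Here the number comes from a 4-month period and the outcome from a 3-month period, and whole 3-month intervals cannot be added to make 4 months. An analyst who follows the text as printed would compare 3-month means with a difference derived over 4 months.

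Any error from this runs in the permissive direction. The margin already equals the whole difference between the two planning estimates, so it has no slack to absorb a change of scale. The Discussion says that a positive result could support shorter programmes, so a threshold wider than intended would matter for patients who self-harm.

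**Working it through.** **Inputs.** From Sample size and power analysis: 2.26 and 0.73 episodes over 4 months, pooled SD 4, alpha .05, power .80, 85 per group, 120 recruited per group. From Comparison of DBT-6 versus DBT-12: a one-sided test. From Primary outcome and Table 1: a 3-month window. The true difference is taken as 0, in line with the stated expectation of no difference between arms. The 3-month SD is not given, so it is varied.

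**Step 1: the plan's own figures.**
- Margin: 2.26 − 0.73 = 1.53.
- Sample size: n per arm = 2(1.645 + 0.842)² × 4² / 1.53² = 84.5, so 85. This matches the plan.
- A one-sided alpha of .025 would give 108, which does not match. With an SD of .04 the formula gives 1 per group, so .04 cannot be the SD used.

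The stated 85 therefore rests on a margin of 1.53 and an SD of 4. Both are printed with the 4-month estimates.

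**Step 2: change of window, assuming a constant event rate.**
- 1.53 per 4 months = 1.53/4 = 0.3825 per month = 1.53 × 3/4 = 1.1475, about 1.15, per 3 months.
- 1.53 per 3 months = 1.53 × 4/3 = 2.04 per 4 months.
- Ratio: 1.53/1.1475 = 1.33.

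**Step 3: chance of declaring non-inferiority if 1.53 is applied unscaled and the true excess is 1.1475 per 3 months.** Two-sample normal approximation: P = Φ[(1.53 − 1.1475)/(SD√(2/n)) − 1.645]. The three SDs are 3.0 (scales with time, 4 × 3/4), 3.46 (scales with the square root of time, 4 × √0.75) and 4 (unchanged).

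| 3-month SD | n = 85 per arm | n = 120 per arm |
|---|---|---|
| 3.0 | Φ(0.831 − 1.645) = 21% | Φ(0.988 − 1.645) = 26% |
| 3.46 | Φ(0.720 − 1.645) = 18% | Φ(0.855 − 1.645) = 21% |
| 4.0 | Φ(0.623 − 1.645) = 15% | Φ(0.741 − 1.645) = 18% |

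With the margin set at 1.1475, each entry would be 5%.

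**Step 4: power with the margin at 1.1475, 85 per arm and true difference 0.** Power = Φ[1.1475/(SD√(2/85)) − 1.645]; n for 80% power = 2(1.645 + 0.842)² SD² / 1.1475².

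| 3-month SD | Power at 85 per arm | n per arm for 80% |
|---|---|---|
| 3.0 | 80% | 85 |
| 3.46 | 70% | 113 |
| 4.0 | 59% | 151 |

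**The case against.** The strongest reply is that no sentence in the article says 1.53 will be compared with 3-month means. The sample size paragraph also speaks of rates, and a fitted Poisson model can express its means per 3 months, per 4 months or per month. The statistical analysis plan, not shown here, may do this. That stands as a limit on the consequence. It does not remove the mismatch: the article names no denominator for its rates, and a reader who takes it at its word has a 4-month difference and a 3-month outcome.

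Second, only the planning estimates carry the 4-month label. The sponsor may have meant 1.53 per assessment as the clinical limit. Against that limit the test keeps its 5% error, and the 15–26% figures arise only if the intended limit is 1.15 per 3 months. This is fair, and those figures should not be read as the trial's actual error rate. However, the only derivation the article offers for 1.53 is the 4-month difference, which does not support 1.53 per 3 months.

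Third, the factor of 4/3 assumes a constant event rate, and rates may well change with treatment. This also stands.

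Fourth, a reader might infer that the trial is underpowered, or that an SD of .04 undermines the sample size. The documents support neither. If the SD scales with time, power stays at 80% with 85 per arm. The .04 is a misprint, because 85 follows from an SD of 4.

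**Conclusion.** The point holds as a mismatch of time scales in the definition of the primary decision threshold. The margin and the 85 per group were derived on a 4-month scale, the outcome is counted over 3 months, and the article neither gives the margin a time unit nor links the two windows. That much is certain from the text.

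The size of the effect is conditional. If 1.53 is applied unscaled and rates are roughly constant, the margin is one third wider than the difference it came from. The false-positive rate at that intended limit is then about 15–21% with 85 per arm or 18–26% with 120, for a 3-month SD of 3 to 4. These rates come from a simple two-sample approximation, not the planned multilevel model. It would go too far to say that the margin is a third too lax without these conditions, since the documents state neither of them. The effect on power depends on an SD that the documents do not give, and it may be nil.

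**What to change.** Before analysis, put margin and outcome on one time scale and state the unit. Either of these would do:
- set the margin at 1.15 episodes per 3 months (0.3825 per month) and compare it with 3-month marginal means; or
- estimate model-based rates with log time observed as an offset, and compare the difference, expressed per 4 months, with 1.53.

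If the sponsor means 1.53 per 3 months, it should say so and justify that limit on grounds other than the 4-month planning figures.

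Restate power on the chosen scale with its assumed SD, and correct the SD printed beside the margin from .04 to 4. The correction does not alter the sample size.

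The cost is wording in the protocol or analysis plan, with no new data. Enrolment is complete at 240, so if the 3-month SD proves nearer 4 than 3, the stated power will be lower and cannot be recovered by recruiting more participants.

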## Methods/design

### Study aims and hypotheses

#### Aim 1

To evaluate the clinical effectiveness of DBT-6 compared to DBT-12 for the treatment of chronically self-harming individuals with BPD. The following main hypotheses will be examined:

**Hypothesis 1a**: Patients in the DBT-6 arm will show equivalent reductions in the frequency and severity of self-harm across the treatment phase compared with patients in the DBT-12 arm. **Hypothesis 1b**: Patients in the DBT-6 arm will show equivalent reductions in the frequency and severity of self-harm across a 1-year post treatment follow-up phase, compared with patients in the DBT-12 arm.

#### Aim 2

To identify which subtypes of BPD patients are as likely to benefit from DBT-6 versus DBT-12.

**Hypothesis 2a:** Patients who present with high rates of self-harm and impulsive behaviours will have reductions in the frequency and severity of self-harm behaviours that are comparable in the DBT-6 arm and the DBT-12 arm, over the course of both the treatment phase and the 1-year post treatment follow-up.

**Hypothesis 2b**: Patients with co-occurring post-traumatic stress disorder, generalized anxiety disorder, or cluster A or C personality disorders will exhibit lesser reductions in the frequency and severity of self-harm behaviours in the DBT-6 arm compared to the DBT-12 arm, over the course of both the treatment phase and the 1-year post treatment follow-up. In other words, a subtype by duration interaction is expected.

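### The non-inferiority sample size does not establish power for the secondary analyses, least of all for the Aim 2 subtype-by-duration interactions

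*Protocol article*

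**What the plan says.** The Protocol article, *Sample size and power analysis*, sizes the trial for one comparison: non-inferiority of DBT-6 to DBT-12 on self-harm frequency. The assumed values are given as "Post-treatment suicide and self-harm estimates over 4 months were 2.26 episodes for DBT-6 and 0.73 for DBT-12", with a pooled SD of 4. The margin is set "as a difference in outcomes of 1.53 (SD = .04) episodes in the frequency of self-harm episodes at post-treatment". The result is stated as "α = .05; 1 - β = .80), 85 participants per group are required to show non-inferiority of treatment", raised to 120 per group for 30% dropout.

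The paragraph then makes a second claim: "The sample size calculation also addresses the necessary power for secondary analyses". The reason given is that "the sample size required for null hypothesis significance testing is typically less than those required for non-inferiority".

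The section headed *Secondary analysis* consists of the Aim 2 subtype analyses. Under *Study aims and hypotheses*, Hypothesis 2b predicts smaller reductions in self-harm on DBT-6 for patients with PTSD, GAD, or cluster A or C personality disorders, and adds: "In other words, a subtype by duration interaction is expected". *Secondary analysis* names these four diagnostic groups and applies a Holm adjustment to the pairwise comparisons. The article gives no interaction size, subtype prevalence or power figure for these tests.

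**The concern.** The general statement that significance tests need fewer patients than non-inferiority tests is true when the effect sought is larger than the margin. Here the margin was set equal to the entire difference assumed between the arms, so the usual saving is absent. The analyses the sentence is meant to cover are also mainly interactions. These are estimated with much less precision than a main effect from the same patients.

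What is at stake is how the Aim 2 results are read. The Background says that knowing how treatment length works for subsets of patients should affect how they are triaged. Hypothesis 2a expects comparable results for one subtype, while Hypothesis 2b expects a difference for others. A reader told that these analyses have the necessary power could take a non-significant interaction as evidence that a subtype does as well on 6 months. The design may have had little chance of showing otherwise.

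**Working it through.** **Inputs from the Protocol article.** Difference and margin: 2.26 − 0.73 = 1.53. SD = 4 (the pooled value; the .04 printed beside the margin does not reproduce the stated sample size). α = .05, power .80. True difference under non-inferiority taken as 0 ("We expected no significant differences between the DBT-6 and DBT-12 conditions"). Primary test one-sided ("1-sided non-inferiority t-tests of the marginal means will be performed"). Recruited: 120 per arm.

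**1. Reproduce the plan's figure.** n per arm = 2(z₁₋α + z_power)² SD² / margin².
- One-sided .05: 2(1.645 + 0.842)² × 16 / 1.53² = 84.5, so 85. This matches the plan.
- With 30% dropout, 120 × 0.7 = 84 completers per arm.

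**2. Significance test for the same 1.53 and SD 4.**
- One-sided .05: the formula is identical, so 85.
- Two-sided .05: 2(1.960 + 0.842)² × 16 / 1.53² = 107.3, so 108.
- On these inputs a significance test never needs fewer patients than the non-inferiority test.

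**3. Two-sided power of the main comparison for 1.53.** SE = 4√(2/n).
- n = 85: SE = 0.614; Φ(1.53/0.614 − 1.960) ≈ 70%.
- n = 120: SE = 0.516; Φ(1.53/0.516 − 1.960) ≈ 84%.

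**4. Standard error of an interaction.** Let a proportion p of each arm have the subtype, with the same SD throughout. Then SE_int = 4√(2 / (n p(1 − p))), which is the main-comparison SE divided by √(p(1 − p)). Since p(1 − p) is at most 0.25, SE_int is at least twice the main SE. The same effect size therefore needs at least four times the sample, whichever sidedness is used.

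**5. Illustrative sample size per arm for an interaction of 1.53, 80% power.** The interaction size and prevalences are assumptions; the plan gives neither.

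| Test level | p = 50% | p = 20% |
|---|---|---|
| One-sided .05 | 84.5/0.25 → 339 | not calculated |
| Two-sided .05 | 107.3/0.25 → 430 | 107.3/0.16 → 671 |
| Two-sided .0125 (first Holm step if the family is four tests) | 610 | 953 |

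**6. Illustrative power for an interaction of 1.53 at p = 50%.**

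| n per arm | SE_int | Two-sided .05 | One-sided .05 |
|---|---|---|---|
| 85 | 1.227 | Φ(1.247 − 1.960) ≈ 24% | Φ(1.247 − 1.645) ≈ 35% |
| 120 | 1.033 | Φ(1.481 − 1.960) ≈ 32% | Φ(1.481 − 1.645) ≈ 44% |

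**7. Smallest interaction detectable with 80% power, two-sided .05, p = 50%.** (1.960 + 0.842) × SE_int:
- n = 85: 2.802 × 1.227 ≈ 3.4 episodes.
- n = 120: 2.802 × 1.033 ≈ 2.9 episodes.

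Both exceed the whole post-treatment mean of 2.26 assumed for DBT-6 and are about twice the margin.

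**The case against.** Several points on the other side are fair.

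- **Sidedness.** A reader might infer that the plan's own figures require 108 per arm instead of 85. They do not. The article states no two-sided level for the secondary tests, its primary test is one-sided, and Hypothesis 2b is directional. The whole gap between 85 and 108 comes from sidedness. What remains is that the significance test needs no fewer patients, which is enough to defeat the stated reason.
- **The main comparison.** A reader might infer that it is underpowered for a two-sided test. That depends on dropout. The analysis is by intention to treat and 120 per arm were randomised; if all are analysed, two-sided power for 1.53 is about 84%.
- **The interaction figures.** A reader might take 430 per arm as a requirement, or 24–32% as the best attainable power. Neither is supported. The 430 rests on an assumed interaction of 1.53, 50% prevalence and a two-sided test; an interaction near 3.4 episodes would need only about 85 per arm. One-sided testing alone raises power to 35–44%. The planned growth models use repeated assessments and over-dispersed Poisson forms, so a cross-sectional comparison of means cannot bound their power in either direction.
- **Holm.** The article does not define a family of four tests, so the .0125 row is also an assumption.
- **The quoted clause** is a hedged general statement, and the 85 itself is correct. The fault lies in applying the generality here.
- **Harm.** The article nowhere says that a null interaction would be read as equal benefit. That is a risk of interpretation, not a stated plan.

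These points limit the numbers. They do not restore the claim that the sample size calculation covers the secondary analyses.

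**Conclusion.** The point holds in a limited form: the reason given for secondary-analysis power is wrong for this design. This follows from the plan's own margin, assumed difference and SD, with no added assumption.

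For the main comparison, any shortfall against two-sided testing is conditional on how many patients are analysed. For the Aim 2 interactions the gap is clear. With equal SDs and the same subtype share in each arm, their standard error is at least double that of the comparison the trial was sized for. Only an interaction of roughly 2.9–3.4 episodes would reach 80% power in the most favourable prevalence case (two-sided). All interaction figures rest on the plan's normal-means approximation with SD 4 and on assumed prevalence; the sample sizes and power figures also assume an interaction of 1.53. The planned models could change them. They show the order of magnitude and are not a substitute power calculation.

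**What to change.** In *Sample size and power analysis*, delete the sentence on secondary analyses. In its place:

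- State that the trial was sized only for the primary non-inferiority comparison, and that 80% power is not established for the Aim 2 interactions.
- Give the illustrative power (about 24–32% two-sided or 35–44% one-sided with 85–120 per arm) together with its assumptions: interaction of 1.53, SD 4, 50% prevalence, no Holm adjustment, cross-sectional normal means. Note that lower prevalence or a Holm adjustment reduces it and that the repeated-measures Poisson models may change it.

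In *Secondary analysis*, commit to reporting each interaction estimate with its confidence interval, and state that a non-significant interaction is not evidence that a subtype does equally well on 6 months.

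The cost is one rewritten paragraph and one added statement. Enrolment is complete, no patients are added, and the primary analysis is unaffected. The price is a less favourable statement about Aim 2.
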